# Methods

The study is an assessor blinded, randomized controlled trial. Patients are randomized by simple drawing. For logistic reasons, an exercise team consists of ten patients. The letters A and B are equally distributed in 20 envelopes, and represents the physical exercise intensity. The sealed envelopes are all put into a larger envelope from where the patients will draw one envelope at randomization.

[figure not shown]
A total of 60 patients with paroxysmal/persistent AF will be included, using consecutive sampling, from the Department of Cardiology, Copenhagen University Hospital Hvidovre. After inclusion, baseline tests will be performed as follows: physical capacity measured on Six Minute Walk Test and maximal physical capacity measured on ergometer bike, Figure 1. Patient characteristics, medication, risk factors and comorbidity will be registered. Before the exercise intervention, all participants will complete a nurse-led rehabilitation program regarding AF. The patients will then be randomized to either low intensity physical exercise (50% of maximum physical exertion) or high intensity physical exercise (75-85% of maximum physical exertion).

The exercise intervention lasts 12 weeks with exercise sessions twice weekly of 60 and 90 minutes duration, respectively. They consist of cardiovascular exercise (cycling, running) and will be supervised by cardiac physiotherapists. Intensity is measured as perceived exertion on Borg 20 scale introduced at the initial sessions. The exercise sessions will be conducted at the hospital.

During the intervention and two months after the last exercise session, the patients upload an electrocardiogram (ECG) from a handheld ECG-device twice daily and in case of symptoms of AF.

One year after the intervention is completed the patients will be invited to a follow-up. During the follow-up time all hospital admissions are registered from the medical records.

At baseline and after the 12-week intervention, blood samples will be taken and stored in a bio bank for later analyses. A total of 90 mL. blood per participant will be drawn. The blood samples will be stored anonymously at minus 80 degrees Celsius for 10 years for future research.

The trial is expected to start in October 2012 with end of follow-up one year after the last exercise session.

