## Inclusion and exclusion criteria

Inclusion criteria:

1. Male or female aged ≥ 18 years
2. AF documented on ECG
3. Written informed consent

Exclusion criteria:

1. Significant language barrier
2. Severe illness with an expected survival less than one year
3. Permanent AF
4. Signs of significant cardiac comorbidity during initial testing requiring treatment (ischemic heart disease, severe aortic stenosis).

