# Sample size

The aim of our trial is to study whether high intense physical exercise reduces burden of AF more than low intense physical exercise. Our primary outcome, burden of AF, is assessed as total number of ECGs with AF. We expect to reduce the burden of AF with 25%. The patients send an ECG twice daily and in case of symptoms which will sum up to 300 ECG per patient. We assume that total number of ECGs with AF in the low intense group will be 20 compared to 15 in the high intense group. The estimated power will be 94.3% for α=0.05 (two-sided 95% CI) and SD=6, which is higher than the generally accepted power of 80%.

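### The 60 patients are counted before testing and randomisation, while the 94.3% power needs all 60 randomised with full data, and even then reproduces only with a one-sided critical value

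*Protocol*

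**What the plan says.** The Methods section of the protocol sets the target: "A total of 60 patients with paroxysmal/persistent AF will be included, using consecutive sampling". The sequence follows:

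- "After inclusion, baseline tests will be performed as follows", naming the walk test and the ergometer test.
- Next comes the rehabilitation programme, which every participant is to finish before exercise starts.
- Allocation comes last: "The patients will then be randomized to either low intensity physical exercise" or to the high-intensity arm.

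On allocation, Methods says "The letters A and B are equally distributed in 20 envelopes". Three full sets make 60.

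The fourth exclusion criterion reads "Signs of significant cardiac comorbidity during initial testing requiring treatment", with ischaemic heart disease and severe aortic stenosis as its examples. Ethical considerations has consent signed at inclusion.

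The Sample size section assumes 20 ECGs with AF in the low-intensity arm and 15 in the high-intensity arm, and concludes: "The estimated power will be 94.3% for α=0.05 (two-sided 95% CI) and SD=6". It compares this with a benchmark of 80%. It states no number of patients, no expected loss and no replacement rule.

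**The concern.** Two things do not fit together.

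First, the target of 60 is attached to inclusion, and a step that can remove patients lies between inclusion and the draw. If recruitment stops once 60 have been included, the number randomised may be smaller. What the target counts decides when recruitment ends, so the protocol has to settle it.

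Second, the power figure leaves no room for such losses. It corresponds to 60 patients randomised and analysed, and only if a one-sided critical value is used. At the stated two-sided level, the figure is not reached even if nobody is lost. The margin over 80% is therefore smaller than 94.3% suggests, and every loss, before or after randomisation, draws on it.

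**Working it through.** **Inputs.** Difference 20 − 15 = 5, SD 6, α = 0.05, stated as two-sided (Sample size). The total of 60 comes from Methods, as Sample size gives none. Equal allocation, 30 per arm, comes from the envelope scheme.

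**Reproducing the printed figure.** For n per arm, the normal-approximation power is Φ(δ / (SD·√(2/n)) − z). With n = 30:

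- Standard error = 6 × √(2/30) = 1.549, and 5 / 1.549 = 3.227.
- Two-sided, z = 1.960: Φ(1.267) = 89.8%. The noncentral t calculation gives 88.8%.
- One-sided, z = 1.645: Φ(1.582) = 94.3%. This matches the printed figure.

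So 94.3% is the power of a one-sided 5% test with 30 per arm and no loss. Reaching 94.3% two-sided would take 37 per arm (74 patients) by the normal approximation.

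**Effect of loss.** The protocol gives no rate, so the percentages below are assumptions. Equal arms are used throughout.

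| Analysed | Loss from 60 | Two-sided, t | Two-sided, normal | One-sided, normal (basis of 94.3%) |
|---|---|---|---|---|
| 60 | 0% | 88.8% | 89.8% | 94.3% |
| 57 | 5% | 87.1% | 88.2% | 93.3% |
| 54 | 10% | 85.2% | 86.5% | 92.2% |
| 48 | 20% | 80.7% | 82.3% | 89.3% |
| 45 | 25% | 78.0% | 79.8% | 87.5% |

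**Separating the two causes.** From the printed 94.3% to the two-sided t-test figure for all 60 is 94.3 − 88.8 = 5.5 points. Of these, 4.5 are sidedness (94.3 − 89.8) and 1.0 is the use of t rather than normal (89.8 − 88.8). None of it is loss. A 10% loss then costs 88.8 − 85.2 = 3.6 points, so the total fall is 9.1. A 20% loss costs 88.8 − 80.7 = 8.1 points.

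**Margin to the benchmark.** Two-sided power of 80% needs 23 per arm (46) by the normal approximation or 24 per arm (48) by the t calculation. So 12 to 14 of the 60, or 20% to 23%, can be lost before power drops below 80%.

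**Can the exclusion act on patients already counted?** Consent is signed at inclusion. The only test given a threshold for ischaemia is the ergometer test (ST-depression, under Assessment of outcome), and Methods lists that test after inclusion. Ischaemic heart disease is one of the criterion's own examples. A patient can therefore be included, tested and then excluded before the draw.

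**The case against.** A reader might infer that fewer than 60 patients will be randomised. The protocol does not say so. A patient who meets an exclusion criterion is, in ordinary usage, not among the included, and consecutive sampling could simply continue. Sets of 20 envelopes and teams of ten divide exactly into 60, which fits an intention to randomise 60. The flow figure is not available and may show where the count is taken. The criterion's other example, severe aortic stenosis, points to echocardiography, which is not among the tests that Methods lists directly after inclusion, so initial testing is not shown to be the same as those baseline tests. The rehabilitation programme is a step that everyone is to complete, and loss there is only possible. All of this stands. It limits the claim to an ambiguity: fewer than 60 may be randomised.

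A second tempting inference is that loss of patients explains the fall from 94.3% to figures in the low or mid 80s. At 10% loss it does not: 5.5 of the 9.1 points arise with all 60 analysed.

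Two further arguments carry no weight. The 300 ECGs per patient is a rounded schedule total (12 weeks plus two months, about 84 + 61 = 145 days at two a day, is 290 scheduled). It does not enter the power calculation and says nothing about how many are randomised. A partly drawn last set of envelopes matters little. With 54 randomised, the worst split (30 and 24) gives 84.8% against 85.2% when balanced. With 48, the most extreme split (28 and 20) gives 79.6%, with a chance of about 0.07%.

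What the objection does not answer is the power figure, which is wrong as labelled whichever way 60 is read.

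**Conclusion.** The point holds in two parts of different strength.

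The certain part is the stated power. On the protocol's own inputs, a two-sided test with 60 analysed gives 88.8% (t) or 89.8% (normal), not 94.3%. This rests only on the printed difference, SD and α, and on 30 per arm.

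The conditional part is the count. Methods attaches 60 to inclusion, and an exclusion can act between inclusion and the draw, with no replacement rule or allowance for loss. Fewer than 60 may be randomised, but the documents do not establish that they will be. The cost depends on an assumed loss: about 85% power at 10% and about 81% at 20%. The 80% benchmark is crossed only at roughly 20% to 23% loss, so the consequence is moderate. Nothing here shows the trial to be underpowered on its own assumptions.

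**What to change.** In Sample size, state the number of patients and restate the two-sided power as about 89% for 60 randomised and analysed (88.8% by t-test, 89.8% by normal approximation). Then show the allowance for loss as a separate step: about 85% with 54 and about 81% with 48, with the 10% and 20% losses marked as assumptions. This keeps the correction for sidedness apart from the effect of loss.

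In Methods, state that 60 is the number randomised, and that patients excluded on initial testing or leaving before the envelope is drawn do not count towards it. Replacing them introduces no allocation bias, because no allocation is known at that point.

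The cost is one or two sentences in each section, a less favourable stated power and a few more screening work-ups. By 60 / (1 − loss), randomising 60 would take 64, 67, 71 or 75 included for an assumed pre-randomisation loss of 5%, 10%, 15% or 20%.

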## Inclusion and exclusion criteria

Inclusion criteria:

1. Male or female aged ≥ 18 years
2. AF documented on ECG
3. Written informed consent

Exclusion criteria:

1. Significant language barrier
2. Severe illness with an expected survival less than one year
3. Permanent AF
4. Signs of significant cardiac comorbidity during initial testing requiring treatment (ischemic heart disease, severe aortic stenosis).

## Assessment of outcome

Burden of AF:

By using a handheld ECG device (Zenicor®), the patients transmits an ECG twice daily and in case of symptoms of arrhythmia. An episode of AF is defined as > 10 seconds with irregular frequency and no visible p-waves on ECG. Total number of AF-episodes and time to first AF-episode is registered.

One year after last the exercise session, all hospital admissions related to AF are registered from the medical records; recurrent AF, cardiac failure, stroke, dysregulated antithrombotic treatment or medical side effects, implantation of pacemaker, and surveillance of medical treatment.

Quality of Life:

At baseline and at 12-week follow up the quality of life is assessed using the Short Form 36 (SF36) and European Heart Rhythm Association score (EHRA-score).

Patient characteristics:

Age, gender, ethnicity, BMI, comorbidity, medication, cardiac risk profile (family history, smoking, hypertension, hypercholesterolemia, diabetes, stroke/TCI, claudicatio intermittens, daily physical activity, blood pressure and heart rate.

Physical capacity:

Physical capacity is measured on Six Minute Walk Test and assessment of efficiency on ergometer bike with continuously monitoring of blood pressure and ECG. A ST-depression on ECG is considered significant if it is depressed by 0.1 mV measured 60 ms after the QRS-complex. The ergometer test is considered complete when reaching 85% of maximal expected heart rate.

Cardiac load:

Blood pressure and heart rate are measured for 24 hours at baseline and 12-week follow up. Blood pressure will be reported as mean systolic and diastolic blood pressure during daytime and night time, respectively. Heart rate will be reported as mean, minimum and maximum heart rate, arrests, supraventricular and ventricular ectopic activity and number of AF-episodes.

Echocardiography is reported with standard estimates in accordance with national guidelines. Additionally, left atrium volume (ml/m^2^) will be assessed as well as diastolic function (e’, a’ and E/e’).

Biochemical and genetic markers:

General cardiac blood samples, d-dimer, vitamin D, pro-ANP, pro-BNP, SDF-1α, transforming growth factor (TGF)-β1, matrix metalloproteinase-9 (MMP), tissue inhibitor of matrix metalloproteinase-1 (TIMP-1), clusterin, telomere length, telomerase activity and copeptin. The genetic markers has no clinical consequence. Copeptin will be assessed at Rigshospitalet, Copenhagen, where smaller studies regarding AF currently are running. Telomere length, telomerase activity and fibrotic markers will be analysed by MD, ph.d. [name].

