# Study objectives

1. effect of physical exercise on risk of AF measured on daily electrocardiogram (Zenicor®) during the exercise intervention
2. effect of physical exercise on hospital admissions during one year after the intervention
3. effect of physical exercise on quality of life measured before and after the exercise intervention (SF36 and EHRA-classification)
4. effects of physical exercise on physical capacity measured by 6 Minute Walk Test and on ergometer bike
5. effect of physical exercise on the cardiac work load measured on echocardiography, 24-hour heart rate and rhythm, and blood pressure
6. the predictive value of telomere length, telomerase activity, copeptin and fibrosis markers on exercise effect

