# Hypotheses

1. high intensity physical exercise reduces burden of AF by 20% (number of AF-episodes, time to first episode)
2. high intensity physical exercise reduces hospital admissions by 20%
3. high intensity physical exercise improves quality of life on EHRA-classification and by 20% in minimum five out of eight parameters on SF36
4. high intensity physical exercise increases maximal physical capacity by 20%
5. high intensity physical exercise improves the cardiac work load by reducing the mean heart rate and blood pressure, and improving the diastolic function.
6. a significant association between telomere length and effect of exercise as well as increased telomerase activity after the exercise intervention.

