# Outcomes

1. Primary outcome is number of AF-episodes during and after the exercise intervention measured on handheld ECG (Zenicor®)
2. Secondary outcomes are:
3. time to first AF-episode
4. change in maximal physical capacity measured on Six Minute Walk Test and ergometer bike
5. change in heart rate, blood pressure and cardiac load measured on echocardiography
6. change in quality of life
7. Tertiary outcomes are:
8. Number of hospital admissions with AF or complications to AF
9. Death
10. Change in biochemical markers

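### The 24-hour rhythm recording is summarised for AF only by a count of episodes, which can move opposite to the amount of AF; percentage of recorded time in AF should be the summary

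*Protocol*

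**What the plan says.** Study objectives, item 5, includes "24-hour heart rate and rhythm" among the measures of cardiac work load. Assessment of outcome, under Cardiac load, gives the timing: "Blood pressure and heart rate are measured for 24 hours at baseline and 12-week follow up". It then lists what is taken from the recording: "Heart rate will be reported as mean, minimum and maximum heart rate, arrests, supraventricular and ventricular ectopic activity and number of AF-episodes". Nothing else in that list measures AF.

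The only definition of an episode stands earlier in the same section, under Burden of AF, next to the description of the handheld device: "An episode of AF is defined as > 10 seconds with irregular frequency and no visible p-waves on ECG". It sets a minimum length, no maximum, and no weighting by length. No separate definition is given for the 24-hour recording.

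On the population, Methods states: "A total of 60 patients with paroxysmal/persistent AF will be included". The only AF type excluded is permanent AF.

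**The concern.** A continuous recording can show directly how much of the day is spent in AF. The protocol reduces it to a count, which reflects how often the rhythm switches. One short run and one unbroken day of AF each add at most 1. A patient whose short bouts merge into continuous AF would show fewer episodes at 12 weeks than at baseline. A patient whose bouts shorten without a matching gain in the sinus intervals would show more.

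What is at stake is the reading of the AF part of objective 5. A change in the count from baseline to 12 weeks cannot by itself be read as more or less AF, although the recording holds the information that would settle it.

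**Working it through.** The protocol gives no figure for the 24-hour count, so there is nothing of its own to reproduce. Its sample-size figures concern the handheld ECG and do not bear on this point. It also gives no bout or interval lengths, so all lengths below are assumptions chosen for illustration.

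**Formulas.** Let A be the length of an AF bout and S the length of the sinus interval between bouts, in hours.
- Episodes per day (long-run rate) = 24/(A + S)
- Share of time in AF = A/(A + S)

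**Worked cases.**

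| Change | Episodes per day | Time in AF |
|---|---|---|
| A from 4 to 3, S = 4 | 24/8 = 3.00 to 24/7 = 3.43 | 4/8 = 50% to 3/7 = 43% |
| A from 1 to 12, S = 5 | 24/6 = 4.00 to 24/17 = 1.41 | 1/6 = 17% to 12/17 = 71% |
| Four 30-minute bouts to continuous AF | 4 to 1 | 2/24 = 8% to 100% |

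In the first row AF decreases and the count rises. In the other two AF increases and the count falls. The value 1 in the last row is the most that an all-AF recording can score; it would be 0 if only onsets within the window were counted.

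**When the reversal occurs.** The long-run count depends on A + S only. If bouts shorten, the count falls only when the sinus interval grows by more than the bout shrinks. With A from 4 to 3 and S from 4 to 5, the count is 24/8 = 3.00, unchanged, while time in AF falls from 50% to 3/8 = 37.5%. With a longer S the count falls too, in line with time in AF. If bout length does not change, fewer episodes does mean less AF.

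**Check with random lengths.** Recordings of 24 hours were simulated with exponentially distributed bouts and intervals, 20,000 per scenario, counting bouts over 10 seconds.

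| Mean A, mean S (h) | Episodes | Time in AF |
|---|---|---|
| 2, 4 (reference) | 4.3 | 33% |
| 0.5, 4 | 5.4 | 11% |
| 0.5, 2.5 | 8.1 | 17% |
| 0.25, 2 | 10.7 | 11% |
| 6, 4 | 3.0 | 60% |
| 12, 4 | 2.2 | 75% |
| 24, 4 | 1.7 | 86% |
| 200, 1 | 1.1 | 99.5% |

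The simulated counts slightly exceed 24/(A + S) because a bout already in progress at the start is counted. For the reference, 24/6 + 2/6 = 4.33, which agrees with 4.3. Against the reference, each scenario with less AF has more episodes and each with more AF has fewer. The scenarios were chosen to show the mechanism; they do not estimate how common it is.

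**The case against.** The strongest objection is that this count carries little weight in the trial. The Outcomes section assigns an episode count to another device: "Primary outcome is number of AF-episodes during and after the exercise intervention measured on handheld ECG (Zenicor". Its nearest secondary item covers heart rate, blood pressure and echocardiographic load and does not name AF on the 24-hour recording. Hypothesis 5, the counterpart of objective 5, covers only mean heart rate, blood pressure and diastolic function. No test and no direction of benefit is stated for this count. That largely stands. It is not complete, because objective 5 names rhythm and the secondary item on heart rate is spelled out under Cardiac load by a list that contains the count.

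A reader might infer that the trial will score harm as benefit. The protocol does read fewer episodes as less burden in hypothesis 1, "high intensity physical exercise reduces burden of AF by 20% (number of AF-episodes, time to first episode", but that hypothesis matches objective 1, which concerns the handheld ECG. Carrying its direction over to the 24-hour recording is an inference.

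A reader might also infer that an 11-second run on the 24-hour recording formally counts as an episode. The 10-second rule is given with the handheld device, so applying it here is plausible but not stated. The argument does not need it, since any count without weighting by length behaves the same way.

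Finally, a reader might take this recording to be the trial's only AF measure free of patient choice, or extend the criticism to the primary outcome. Neither is supported. Twice-daily handheld ECGs over 12 weeks plus two months are about 145 days × 2 = 290 scheduled recordings, of the roughly 300 per patient that Sample size assumes. Patients may choose the hour, but most recordings are not triggered by symptoms. As sized, that outcome is ECGs showing AF ("total number of ECGs with AF in the low intense group will be 20 compared to 15"), and the number of scheduled ECGs with AF rises with time in AF.

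**Conclusion.** The point holds as a limited one. The protocol itself fixes an episode count as the sole AF summary of a continuous recording, in a population where all-AF recordings are possible. That count can move opposite to the amount of AF. The possibility follows from counting without regard to length; the illustrated sizes (for example 8% to 100% of the day with the count going from 4 to 1) rest on assumed bout and interval lengths. The frequency of reversal cannot be derived from the protocol, and nothing shows it to be likely. The consequence is confined to a supporting measure under objective 5. The primary outcome, the sample size and the trial's main conclusion on AF are not affected. The change is still worth making because the better summary comes from the same recordings at almost no cost.

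**What to change.** In Assessment of outcome, under Cardiac load:
- Make percentage of recorded time in AF the AF summary of the 24-hour recording, with an all-AF recording entered as 100%.
- Keep the number of episodes as a descriptive item beside it, and say which episode definition applies to this recording.
- Base any comparison of arms on AF from this recording on the percentage. Take baseline into account with a method that tolerates many values at 0% and 100%, for example a rank-based one. One 24-hour window per visit in this population may produce many such values, which suits an ordinary linear model with baseline as covariate poorly.

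The cost is a wording change and one extra readout from the same recordings, with no new visit or procedure. A rank-based comparison gives a less direct statement of effect size, so the percentages should be shown by arm and visit as well.
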